### Statistical methods

Participant attributes will be analysed using descriptive and inferential statistics to assess baseline comparability among the 3 treatment groups. Comparison of differences between the 3 groups in the randomised controlled trial will be analysed using multiple regression analysis, with statistical significance set at p < 0.05. Statistical analysis in RCT1 will be conducted using 2 group comparisons on all participants, based on the BBT (T1 vs T2). Data from all randomised participants will be conducted on an intention to treat basis. Where outcome data are unavailable, previous scores will be carried over for analysis. Statistical analysis for RCT2 will be conducted at 2 weeks (T3) and 10 weeks (T4) compared to (T1) baseline scores, analysing between group differences. Primary analyses at T3 and T4 will be based on the COPM and GAS scores. Secondary analysis will use the same data analytical methods for scores on the BBT and range of motion for T3 only.

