Preliminary evidence suggests that functional hand splints may have an immediate positive effect on hand function [18], and provide a supplementary effect to goal directed training [19]. Whilst splints may provide a very small clinical effect, it is unclear whether this leads to any improvement in function [13], and evidence suggests this immediate improvement may not be maintained beyond the splint-wearing period [13]. There is no reliable evidence to support the use of hand splints as a therapeutic modality in isolation of other intervention approaches [13]. In addition to splinting to reposition the hand, the patient may also be trained to use their hand in a functional way using a task-specific training approach.

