### Study procedures

Figure 1 depicts the study procedure. Informed consent will be obtained following screening for eligibility criteria. Baseline assessment, using the COPM, GAS, BBT and wrist range of motion will be completed within 3 weeks of treatment (T1). Following baseline assessment, participants will be randomly allocated to one of 3 treatment groups:

1. Functional hand splint alone.

2. Task-specific training (CO-OP) combined with functional hand splint.

3. Task-specific training (CO-OP) alone.

Participants allocated to a group involving a functional hand splint will have a customised hand splint fabricated immediately following randomisation. One hour following baseline assessment, the box and blocks test will be repeated with participants allocated to the functional hand splint alone (with splint on) or task-specific training alone (no splint) group (T2). This data will be used to investigate the immediate effect of a functional hand splint (RCT1). All participants will then undertake 2 weeks of treatment, according to group allocation. The functional hand splint alone group will be expected to wear the splint for 1 hour of daily practice of goals. Task-specific training will involve 10 daily one hour sessions of CO-OP conducted over 12 consecutive days. CO-OP will be undertaken within a group of 2-4 participants. Children allocated to the task-specific training (CO-OP) combined with functional hand splint will be expected to wear their hand splint at all times during the 10 sessions of CO-OP. Assessment at the end of the 2 weeks of treatment (T3) will involve the COPM, GAS, Box and blocks test and wrist range of motion. Log books of home practice will be completed by all participants. Participants will not be expected to continue practice of goals beyond the 2 week treatment timeframe. Participants will be asked to complete a log book of practice if they choose to continue to utilise the functional hand splint or practice goals using those strategies from CO-OP intervention. Follow up assessment, using the primary outcomes only (COPM and GAS) will occur at 10 weeks following baseline assessment (T4).

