##### The goal attainment scale (GAS)

The GAS is a measure of change of client-specific goals that may not be measurable through standardised assessments [50,52]. The GAS may offer children and families the opportunity to set a wider range of goals than those set using the COPM, particularly in regard to upper limb activities [50]. Following the administration of the COPM, 3 GAS goals related to upper limb function will be set. Goals will be formatted on a 5 point scale; -2 (current level of function); -1 (less than expected level of performance); 0 (expected level of performance), +1 (more than expected level of performance); +2 (much more than expected level of performance). Whilst being recognised as being responsive to change [50], there is still limited evidence supporting the reliability and validity of GAS for detecting clinically significant changes [52,53]. A change of 2 points on the GAS is generally recognised as significant (ie. a change from -2, current level of function to 0, expected level of performance) [53].

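### Carrying previous scores forward fills a missing T3 COPM or GAS with baseline and a missing T4 with T3 (or baseline), which can bias the primary group contrasts in either direction

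*Protocol article*

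**What the plan says.** The Statistical methods section of the protocol article gives a single rule for missing outcomes: "Where outcome data are unavailable, previous scores will be carried over for analysis". The filled values enter an all-randomised analysis: "Data from all randomised participants will be conducted on an intention to treat basis". The comparison times are fixed: "Statistical analysis for RCT2 will be conducted at 2 weeks (T3) and 10 weeks (T4) compared to (T1) baseline scores". So are the outcomes: "Primary analyses at T3 and T4 will be based on the COPM and GAS scores".

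Study procedures shows which score is the previous one. COPM and GAS are measured at T1, T3 and T4. At T2, about an hour after baseline, only the Box and Block Test (BBT) is done, and only in two of the three arms: "the box and blocks test will be repeated with participants allocated to the functional hand splint alone (with splint on") or training alone (no splint). The last visit is limited too: "Follow up assessment, using the primary outcomes only (COPM and GAS) will occur at 10 weeks following baseline assessment (T4"). The GAS section fixes the starting value of every goal: "Goals will be formatted on a 5 point scale; -2 (current level of function").

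The article states no other handling of missing outcomes, no sensitivity analysis and no expected dropout rate.

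**The concern.** All three arms receive an active treatment, so improvement between T1 and T3 is plausible in each. Filling a missing T3 with T1 records that child as having made no progress. Filling a missing T4 with T3 assumes that nothing changed in the weeks after treatment, which is the question T4 is there to answer. The protocol does not expect practice to continue after the two weeks.

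At stake are the between-group contrasts on both primary outcomes at both primary times. Shrinkage is not a safe direction here. Hypothesis 1 predicts that the combined arm and training alone will improve to a similar degree, so a rule that pulls a real difference towards zero favours that hypothesis. With 15 children per arm, one child is 6.7% of an arm, so a few lost visits are enough to matter.

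**Working it through.** **Inputs from the protocol article (Sample size).** 15 per group, 80% power, effect size 0.9, target difference 2 COPM points. The implied SD is 2 / 0.9 = 2.22.

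**The plan's own figure.** By the normal approximation, an effect size of 0.9 needs 20 per group two-sided at 0.05 (power at 15 is 69.3%), or 16 one-sided (79.4% at 15). Two-sided with covariates explaining 25% of the variance gives 15. Neither the sidedness nor the variance explained is stated, so 15 is reproduced only under one of these variants. That is a separate matter; here the figure supplies only n and the SD.

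**Assumed, because the document gives no value.** Gains by arm, and missing fractions of 0 to 27% per arm (27% is about 4 of 15, 7% about 1 of 15).

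**Step 1: what gets filled (COPM and GAS).**

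| Missing | Filled with | Meaning |
|---|---|---|
| T3 | T1 | no improvement; GAS = -2 |
| T4 only | T3 | no change after treatment |
| T3 and T4 | T1 at both | no improvement at either time |

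**Step 2: expected difference at T3.** With gain g and missing fraction d in each arm, and loss unrelated to outcome within arm, the filled difference is (1 - d1)g1 - (1 - d0)g0.

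- Real difference, equal loss (gains 3 v 1, 20% each): 0.8 × 3 - 0.8 × 1 = 1.6 instead of 2.
- No real difference, gain 3 in both arms, 20% v 5%: 2.40 - 2.85 = -0.45, which is 22% of the 2-point effect.
- The same with 20% v 0%: 2.40 - 3.00 = -0.60, which is 30%.
- Per child at gain 3: 3 / 15 = 0.2 points off the arm mean.
- GAS, with the 2-point change the document treats as significant in both arms, 20% v 5%: 0.80 × 2 - 0.95 × 2 = -0.30 GAS points.

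**Step 3: expected difference at T4 when only T4 is missing.** The arm mean gain is (1 - d)g4 + d·g3.

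- T3 gains 1 v 3, T4 gains 1 v 1, 20% of T4 missing in each arm: 1.0 v 0.8 × 1 + 0.2 × 3 = 1.4, a false difference of 0.4.

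**Step 4: simulation.** 8,000 runs per case, two arms of 15, SD 2.22, baseline correlation 0.5, T3-T4 correlation 0.8 (both correlations assumed), regression on group and baseline, two-sided 0.05, loss completely at random within arm. The difference is the second-named arm minus the first.

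| Case | Carry-forward: estimate, rejection | Observed data: estimate, rejection |
|---|---|---|
| T3, gains 2 v 2, missing 13% v 13% | 0.01, 4.8% | 0.01, 4.6% |
| T3, gains 2 v 2, missing 27% v 7% | 0.41, 9.3% | 0.01, 4.9% |
| T3, gains 3 v 3, missing 27% v 0% | 0.79, 17.2% | -0.01, 5.3% |
| T3, gains 1 v 3, missing 20% v 20% | 1.60, 55.3% | 2.00, 65.5% |
| T3, gains 1 v 3, missing 27% v 7% | 2.06, 79.6% | 2.00, 66.5% |
| T4, T3 gains 1 v 3 becoming 1 v 1, T4 missing 20% v 20% | 0.39, 7.3% | -0.01, 5.2% |
| T4, gains 3 v 3 becoming 1.5 v 1.5, T4 missing 27% v 7% | -0.30, 6.5% | 0.00, 4.8% |

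**Step 5: standard errors.** With gains 1 v 3 and 20% missing, the mean SE was 0.733 with carry-forward and 0.801 with observed data. With gain 1 in both arms and 20% missing it was 0.669 against 0.800, and below the 0.708 obtained with no data missing at all.

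On change scores with SD s, the filled variance per arm is (1 - d)s² + d(1 - d)g², over n. The observed-data variance is s² / (1 - d), over n. The first is smaller when g² < s²(2 - d) / (1 - d)². With s = 2.22 this means g below 2.22 × √2 = 3.1 for d near 0, and below 2.22 × √(1.8 / 0.64) = 3.7 for d = 20%. The document's 2-point effect lies inside that range; larger gains can reverse the direction.

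**Step 6: BBT (secondary).** Read literally, the score before T3 is T2 in two arms, with the splint on in the splint-alone arm, and T1 in the combined arm. The Blinding section has T3 measured first with the splint off. The rule could therefore put a splint-on value into a splint-off comparison in one arm only.

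**The case against.** The strongest reply is that the harm is conditional and its size is not in the document. That stands. With equal gains, equal loss and no later change there is no bias, and opposing effects can nearly cancel (2.06 against a true 2 above). A false difference of 0.45 to 0.60 is less than one SE of a 15 v 15 contrast, which is about 2.22 × √(2/15) = 0.81.

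Three stronger readings are tempting, and the document does not support them.

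- *The rule contradicts the plan's own view of retention.* The Hand splinting section says "evidence suggests this immediate improvement may not be maintained beyond the splint-wearing period". That is background on the immediate effect of a splint on hand function. It does not concern COPM or GAS at 10 weeks, or CO-OP. For CO-OP the Background leans towards retention of learnt skills. Setting T4 equal to T3 is an untested assumption, not an internal contradiction.
- *Loss must be unbalanced because CO-OP is more burdensome.* Both arms in hypothesis 1 have the same ten sessions with a parent present, so the argument reaches only contrasts with the splint-alone arm. Every family must be able to commit to the two-week block, and a missed session is not a missed assessment. Unequal loss is possible but not established.
- *Standard errors are always understated.* They are too small relative to the information actually observed, for moderate gains. In the simulation the model SE tracked the carry-forward estimate's own sampling SD (0.733 against 0.737 with gains 1 v 3 and 20% missing), and large gains can reverse the direction.

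It might also be said that missing-data detail belongs in an analysis plan not shown. That does not answer the point: the article does not leave the method open but names one.

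**Conclusion.** The point holds in conditional form. As written, carry-forward is the only stated handling of missing outcomes, and it governs COPM and GAS at T3 and T4. If data are missing and gains differ, loss differs, or scores move after T3, the primary contrasts are biased, and the direction cannot be known in advance.

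The range is 0 with equal gains, equal loss and no later change. In the T3 cases worked here with no real difference and unequal loss, it is about 0.4 to 0.8 COPM points, with type I error of 9% to 17%. Balanced loss of 20% takes 0.4 points off a true 2-point difference and lowers power from 66% to 55%. These figures rest on assumed gains, correlations and missing fractions, and on loss being unrelated to outcome within arm. They show what the rule can do; they do not predict what will happen. The rule should be replaced before the data are analysed.

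**What to change.** Make the primary RCT2 analysis one of the following, keeping all randomised children as far as the model allows:

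- A likelihood-based repeated-measures model with the observed T3 and T4 scores as outcomes, and terms for group, time, group × time and age. Add baseline COPM as a covariate in the COPM model. Use no baseline term for GAS, because it is -2 for every child and carries no information. T1 should not be both an outcome and a covariate. A child with neither T3 nor T4 adds nothing to this model.
- Multiple imputation by arm, using age, MACS level and the other observed scores, which retains those children.

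Both rest on data being missing at random given what is modelled, which is weaker than what carry-forward assumes. Keep carry-forward as a sensitivity analysis only. State that a missing splint-off T3 BBT is not to be filled with the T2 value.

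The cost is a change of wording, slightly more analysis work and somewhat wider standard errors (0.801 against 0.733 in the case of 20% missing per arm with gains 1 v 3). No new data are needed.

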### Sample size

A total of 45 children will participate in the study. Sample size calculations for RCT2 were estimated using data from a 3 group RCT involving children with cerebral palsy [9], based on multiple regression analysis of data using the Canadian Occupational Performance Measure (COPM) accounting for 2 covariates (group allocation and age). Based on an anticipated effect size of 0.9, power analysis for the 3 group RCT determined that 15 participants per group would give an 80% probability of detecting a clinically significant effect of 2 points on the 10 point COPM scale, with statistical significance set at <0.05.

The BBT will be utilised as the primary outcome for RCT1 (the immediate effect of a splint on hand function). The authors felt that the COPM was not an appropriate immediate outcome measure as goal achievement is unlikely to occur immediately, and as such may not provide a true representation of the capacity for a hand splint to have an immediate positive effect on hand function. The BBT test is thought to be a sensitive gross test of hand function. There are studies utilising the BBT in the unilateral cerebral palsy population [42], however there was no previously published homogeneous sample applicable to our study on which to base a sample estimate using the BBT. As such, we were unable to determine an appropriate sample size, and based the sample size according to that set by RCT2. As such, a total of 30 participants will participate in the two group RCT1 (15 participants per group).

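### Neither trial's analysis names the T1 score as a covariate, and randomised groups are to be tested for baseline differences; adjusting for T1 costs about one degree of freedom and is otherwise no less precise than a change score

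*Protocol article*

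**What the plan says.** For RCT2, the Statistical methods section says that group differences "will be analysed using multiple regression analysis, with statistical significance set at p < 0.05", and that "Statistical analysis for RCT2 will be conducted at 2 weeks (T3) and 10 weeks (T4) compared to (T1) baseline scores, analysing between group differences". It lists no covariates. For RCT1 it says "Statistical analysis in RCT1 will be conducted using 2 group comparisons on all participants, based on the BBT (T1 vs T2").

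Model terms appear in two other places. The Sample size section describes a regression on COPM data "accounting for 2 covariates (group allocation and age"). The Participants section adds that Botulinum Toxin A exposure will be considered in the analyses. According to Study procedures, COPM, GAS, BBT and wrist range of motion are all measured at T1. No section says that the T1 value enters a model as a covariate.

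Statistical methods also plans to analyse participant attributes "using descriptive and inferential statistics to assess baseline comparability among the 3 treatment groups".

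**The concern.** Comparing T3 or T4 with T1 within a between-group analysis, and T1 with T2 in RCT1, most naturally means analysing change scores. Group and age are the two terms counted in the sample-size model, which leaves no place for the T1 score.

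Two things are at stake. The first is precision: a change score fixes the coefficient on baseline at 1, whereas a regression estimates it and so cannot do worse apart from the degree of freedom spent. The second is chance imbalance. The sample covers ages 4-15, MACS I-IV and two diagnoses, with 15 children per arm, so the arms may well differ at T1. A change score generally corrects such a difference by too much or too little.

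Significance tests of baseline differences do not help. After proper randomisation any difference is due to chance, and a non-significant result at this sample size says little about whether an imbalance matters.

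**Working it through.** **Inputs from the protocol:** 15 per group; three groups in RCT2 and two in RCT1; effect size 0.9; 2 COPM points; alpha 0.05; power 80%. **Assumed, because the protocol gives neither:** correlation r between baseline and follow-up of 0.3 to 0.7; ratio k = baseline SD / follow-up SD of 0.5 to 1.

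1. **The plan's own figure.** The normal formula is n per group = 2(z_alpha + z_power)² / 0.9².
   - One-sided 0.05: 2 × (1.645 + 0.842)² / 0.81 = 15.3, so 16; power at 15 is 79.4%.
   - Two-sided 0.05: 2 × (1.960 + 0.842)² / 0.81 = 19.4, so 20; power at 15 is 69.3%, or 66.3% by t test.

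   The stated 15 is therefore close to a one-sided calculation. The section does not state sidedness. Nor does it say whether the implied SD of 2 / 0.9 = 2.22 points belongs to follow-up scores or to change scores. That is a separate question; here it means only that there is no fixed starting power to improve on.

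2. **Residual variance.** Set the follow-up SD to 1.
   - Change score: 1 + k² - 2rk.
   - Adjusted for T1: 1 - r².
   - Difference: (1 + k² - 2rk) - (1 - r²) = (k - r)², which is never negative.

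   Adjustment is therefore never less efficient apart from its degree of freedom, and it gains nothing when k = r. Ratio of adjusted to change-score variance:

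   | k | r = 0.3 | r = 0.5 | r = 0.7 |
   |---|---|---|---|
   | 1 (equal SDs) | 0.91/1.40 = 0.65 | 0.75/1.00 = 0.75 | 0.51/0.60 = 0.85 |
   | 0.7 | 0.91/1.07 = 0.85 | 0.75/0.79 = 0.95 | 0.51/0.51 = 1.00 |
   | 0.5 | 0.91/0.95 = 0.96 | 0.75/0.75 = 1.00 | 0.51/0.55 = 0.93 |

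   The reduction is 15-35% with equal SDs and 0-15% with k of 0.5 to 0.7.

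3. **Chance imbalance.** The standard error of a pairwise baseline difference is √(2/15) = 0.365 baseline SD. The chance that one pair differs by more than 0.5 SD is 2 × [1 - Φ(0.5 / 0.365)] = 17%. For at least one of the three pairs it is about 36% (simulation).

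4. **What a change score leaves.** The regression slope of follow-up on baseline is r/k. Given an observed baseline difference D, the change-score contrast is off by (r/k - 1) × D.
   - Equal SDs: -(1 - r)D. For D = 0.5 baseline SD this is -0.35 SD at r = 0.3 and -0.15 SD at r = 0.7.
   - k = 0.5: -0.4D at r = 0.3, zero at r = 0.5, +0.4D at r = 0.7.

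   Its size and sign depend on quantities the protocol does not give. Averaged over randomisations it is zero.

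5. **What a baseline test could detect.** A pairwise difference must exceed about 2.02 × 0.365 = 0.74 SD to reach p < 0.05. The 0.5 SD imbalance in step 3 would not be flagged.

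6. **GAS.** The GAS section sets the current level of function at -2 for every goal. T1 has no variation, so there is neither imbalance to correct nor precision to gain.

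**The case against.** The strongest reply is that the text does not exclude baseline adjustment. Statistical methods lists no covariates and never uses the term change score; comparing with baseline inside a multiple regression could mean T1 as a covariate. Group and age come from the sample-size model, and Botulinum Toxin A shows that the list is open. The article is condensed, and a covariate list may sit in an analysis plan. This stands in part: a reader might infer that the protocol has settled on an analysis without baseline adjustment, and it has not. What remains is that the wording points towards change scores, and that the one stated count of covariates has no room for T1.

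Second, a change score is not an error. It uses the baseline and is unbiased over randomisations. Any upward regression from low starting scores is expected in every arm alike. This stands; the point concerns precision and conditional error, not validity.

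Third, a reader might infer that adjustment would restore the planned power. If 0.9 is in change-score SD units, the test is two-sided and the SDs are equal, power at 15 per arm (pooled residual degrees of freedom) goes from 67% to 85%, 79% or 74% at r = 0.3, 0.5 or 0.7. With k of 0.5 to 0.7 the range is only 67-74%. Equal SDs are doubtful for COPM, because children rate tasks chosen as difficulties and T1 ratings may bunch at the low end. The protocol does not establish any of these conditions.

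Fourth, nothing in the protocol depends on the baseline tests. This also stands: that they would give false reassurance is a risk, not a stated use.

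**Conclusion.** The concern holds as a worthwhile improvement to a valid analysis. The T1 score is collected but nowhere named as a covariate, and the wording for both trials reads most naturally as change from baseline. For COPM, BBT and range of motion, adjustment is at least as precise as a change score apart from about one degree of freedom, and it removes the linear part of the conditional error from imbalance at T1. GAS, the other primary outcome, is unaffected.

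The gain in residual variance is 15-35% with equal SDs and 0-15% with a baseline SD of 0.5 to 0.7 of the follow-up SD. Both ranges rest on an assumed r of 0.3 to 0.7, so no specific recovery of power should be claimed. The inferential baseline tests are stated plainly and are uninformative after randomisation, though no decision hangs on them.

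**What to change.** - **RCT2:** state in Statistical methods that the T3 (or T4) outcome is modelled on group (two indicators), the T1 value of the same outcome and age. This applies to COPM at T3 and T4, and to BBT and range of motion at T3. GAS takes no baseline term. Name Botulinum Toxin A exposure as a covariate if that is what the Participants section intends. MACS level is optional.
- **RCT1:** model T2 BBT on splint group and T1 BBT.
- **Sample size:** make the model described there agree with the analysis model.
- **Baseline comparability:** replace the inferential tests with a descriptive table.

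The cost is wording. The T1 data are already collected. In RCT2 the residual degrees of freedom go from 41 (45 children less intercept, two group indicators and age) to 40; in RCT1 from 28 to 27. Botulinum Toxin A or MACS would use further degrees of freedom. Where k is close to r there is no gain to set against this, but the loss is small.
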